## Abstract

**Background:**

Mental health issues are gaining in importance in society and the economic system. At the same time, the accessibility and stigmatisation of the mental health care system in Germany can obstruct help-seeking behavior and delay early psychotherapeutic interventions. Therefore, new models of care are being established at the interface of company-supported health promotion and conventional health insurance sponsored outpatient care for people developing mental illnesses. Two large industrial companies, in cooperation with two psychosomatic clinics, have recently established a model of “psychosomatic consultation in the workplace“. This new model of care offers the opportunity for a first psychotherapeutic door to door consultation with occupational medicine within the industrial workplace. The main empirical goals of this study are:

1) Describing the differences between patients who use this new diagnostic and therapeutic offer within the industrial workplace vs. patients who visit a conventional regional outpatient clinic, especially in regard to symptom duration and severity, work ability, and demographic characteristics, and

2) A first evaluation of how patients may benefit more from this new model of care compared to those first seen by standard outpatient care.

In the qualitative part of the study, occupational physicians, psychosomatic therapists, involved personnel and select employees of the involved companies will be asked to comment on their experiences with this new approach.

**Methods/Design:**

The implementation study will take place in Ulm and in Stuttgart, with each site looking at one regional conventional psychosomatic outpatient clinic and one psychosomatic consultation offer within the workplace. 70 consecutive patients in each setting will be recruited (overall n = 280). For the cross-sectional study and pre-post comparison we will use established and validated survey instruments (PHQ, SF-12, WAI, MBI, IS) as well as standardized questions about health care use. For data analysis, we will use uni- and multivariate analytical methods. Qualitative data analysis (expert interviews) will be carried out using Mayring’s content analysis method.

**Discussion:**

The results of this study have the potential to provide evidence-based knowledge about an innovative model of psychotherapeutic outpatient care and to further promote tailored solutions for early psychotherapeutic interventions within the worksite.

**Trial Registration:**

DRKS00003184

## Background

In Germany, absenteeism due to mental health issues is on the rise [1]. The proportion of mental health diagnoses related to early retirement is currently 40%, constituting the largest diagnostic group [2]. The reasons for the rise in this category of diagnoses are diverse and often involve a potent combination of personal and occupational stress [3]. Demands for mobility and flexibility in an already intense workplace are increasing when having and keeping a job is often uncertain [4,5]. Although the concept of mental or psychosomatic disorders has become more acceptable in society, the affected usually still have to overcome a "fear threshold" due to stigmatization [6]. Conventional access to the mental health care system, especially for outpatient psychotherapy, is usually connected to long waiting periods which primarily could raise this “fear threshold” and ultimately increase the likelihood of illness chronification [7].

Due to the increasing prevalence of rates of mental disorders among employees and the subsequent shortage of qualified staff [8], most companies in Germany offer workplace health promotion programs and stress management interventions for their employees. These interventionsare intended to reinforce preventive and salutogenic behaviors, while some also address unfavorable working conditions. Although these interventions seem to be effective, they are primarily geared to healthy employees, and therefore fail to adequately address the needs of those who already suffer from mild but clinically relevant psychological disturbances or fully developed mental illnesses [9]. Thus, occupational health care professionals, human resources staff and affected employees need easily accessible and specifically tailored psychotherapeutic consultations for work-related mental health issues. These groups increasingly enforce the creation and implementation of new models of mental health care in the workplace. The specific model considered in detail here is “Psychosomatic Consultation in the Workplace”, a kind of specific consultation-liaison psychosomatic. In Germany, the field of psychosomatic medicine and psychotherapy is a separate medical speciality next to psychiatry, focussing on the relationships of psychological, social and behavioral factors on bodily processes as well as on mental health. Psychodynamic as well as cognitive-behavioral psychotherapy constitutes the main treatment procedure.

Currently, little is known about the profile of utilizers, or about the effects of this new model of care. Therefore, our study aims to assess the following research questions:

1. Are there differences in demographic, clinical and psychometric characteristics between patients who use the consultation offer in the workplace versus patients who use conventional outpatient care? Is this new model of mental health care successful in reaching employees suffering from psychological disorders earlier in the course of their illness, compared to patients who seek help in conventional outpatient care?

2. What changes occur within a three-month follow-up period after using the offer "psychosomatic consultation at the workplace"? Are they different from those of a conventional outpatient clinic?

3. What is the feedback (i.e. appraisals, attitudes, criticism) of persons who are involved with the offer "psychosomatic consultation in the workplace"?

## Methods/Design

### Intervention

The investigation will take place in two areas in southern Germany, each with an established psychosomatic outpatient clinic and a company providing the newly established model of a "psychosomatic consultation in the workplace". This translates into two regions with two groups each, making a total of four settings (2x2 design). 12 weeks after the first contact (baseline, T1) a postal follow-up survey will take place (follow-up, T2). Participants will be consecutively recruited from November 2011 to September 2012.

The offer of a “psychosomatic consultation in the workplace” is based on a consultation-liason model developed in the general hospital and specifically tailored to the needs of occupational medicine within the workplace [10].

This new model of mental health care has been established on a step by step basis within a large automobile manufacturer in cooperation with a local psychosomatic clinic over the last six years [11]. The psychosomatic consultation offer at a company for security systems started in January 2011, in cooperation with the Department of Psychosomatic Medicine and Psychotherapy, University of Ulm. The employees in the first workplace setting (Stuttgart) are mainly referred to psychosomatic medicine by the occupational physicians or the social worker. The employees at the second setting (Ulm) can directly participate in this offer. For all groups (outpatient and workplace), the offer includes the initial consultation, diagnosis, indication, crisis intervention (if needed) as well as support for referral into the existing secondary treatment system.

The Medical Ethics Board of the University of Ulm has given approval for the study. Patient participation is voluntary. Patients can leave the study at any time without consequences. All patients sign an informed consent form. If a participant drops out, care will be continued.

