### Sample size and power calculations

Statistical power analyses was conducted with regard to the work ability index (WAI) [14] as primary outcome. In our regression model we assume that the condition „intervention in the workplace/in the psychosomatic clinic“explains a variance of 5%. This means that at a statistical significance of 5% and a power of 95%, we will need 110 participants in each group (workplace and clinic) with a total sample size of n = 220. Bearing in mind a drop out rate of 20% we will include 280 patients.

The quantities for the main question (research question 1) in this explorative study result from the foreseen time schedule during the funding period and the feasibility of recruitment. We expect a high rate of participation since the "psychosomatic consultation in the workplace" so far has been greatly accepted and appreciated by the employees. In addition, the employees are assured that the collected data will be kept confidential under the supervision of the research group at the university. To increase the response rate for the follow-up survey, there will be a reminder mailing or a phone call.

There are 14 variables to be measured. The two intervention groups consist of employees who use this service within the 10 month recruitment period. One company has a total of 70,000 employees at the participating sites. The other company has about 3,000 employees. The ratio of male to female employees in both companies is about 4:1 with an average age of 43 years. The employees are unevenly distributed to work in research, development, production and administration.

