At time point T2, we will collect as primary outcome work ability (WAI). As secondary outcome we will collect the following target characteristics: type and severity of the disease (PHQ), health-related quality of life (SF-12), work-related stress effects (MBI, IS) and work requirements (KFZA). The main point of research question 2 is to detect whether or not there are significant differences between T1 and T2. The only newly collected data for T2 is patient satisfaction which will be analyzed descriptively. The effects of the setting on the change of the clinical characteristics will be analyzed by multivariate linear regression models with membership in the setting as independent variable and controlling for selection bias by including the propensity scores for the different treatment groups.

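### The design crosses setting type with region, but the research question 2 model has one loosely defined setting term and no region factor

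*Protocol article*

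**What the plan says.** The Intervention section describes a crossed layout: "This translates into two regions with two groups each, making a total of four settings (2x2 design". The Abstract uses setting in the same four-level sense: "70 consecutive patients in each setting will be recruited (overall n = 280".

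The two workplace offers differ. In Stuttgart, employees come mainly through the occupational physician or the social worker. In Ulm access is open: "The employees at the second setting (Ulm) can directly participate in this offer". The car manufacturer's programme was built up over about six years; the one at the security-systems company began in January 2011.

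The sample-size section treats the comparison as two groups. The workplace/clinic condition "explains a variance of 5" per cent, and "at a statistical significance of 5% and a power of 95" per cent "we will need 110 participants in each group (workplace and clinic) with a total sample size of n = 220".

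Under Statistical analysis, the effect on change for research question 2 comes from linear regression "with membership in the setting as independent variable", adjusted for propensity scores. The propensity covariates are age, sex, education, occupational category and previous contacts. Region is not among them. The group models may be binomial or multinomial. The Discussion uses setting with two levels, clinic and workplace.

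**The concern.** Research question 2 asks whether change after a workplace consultation differs from change after a conventional clinic visit. The stated model does not settle which comparison answers it.

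- **Two levels.** The estimate averages a referral-based, long-running offer and a direct-access, recent one, with nothing planned to show whether they differ. Region is also left unadjusted if the cells do not fill as planned.
- **Four levels.** The natural test of the term asks whether any of four units differ. That is not the comparison the study was sized for.

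The primary outcome, the Work Ability Index (WAI), is analysed with this term, so the choice should not be open once data are seen.

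**Working it through.** **1. Inputs.** From the sample-size section: 5% of variance, alpha 5% (sidedness not given), power 95%, 110 per group, 20% dropout, 280 enrolled. From the Abstract: 70 per setting. Expected at follow-up: 280 × 0.8 = 224, or 56 per cell.

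**2. The plan's own figure.** Noncentral F test in linear regression, noncentrality λ = f² × N, 1 numerator df.
- With f² = 0.05/0.95 = 0.0526, a two-sided 5% test needs N = 249 for 95% power. At N = 220 (λ = 11.6) power is 92.3%; at 224 it is 92.8%.
- With 5% read as f² itself, a one-sided 5% test needs N = 218, close to the stated 220.

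The 220 is thus reproduced as a 1-df, two-group calculation, to within rounding only if one-sided. Sidedness is a separate matter.

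**3. Setting with four levels.** Same λ, 3 numerator df, total R² held at 5%.
- N = 220: power 81.8%. N = 224: 82.6%.
- N needed for 95%: 331.
- If 5% is read as f²: 79.6%, 80.4% and 348 respectively.

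**4. Setting with two levels, cells as planned.** Let p be the Stuttgart share of an arm and δ an additive regional difference in change. The bias in the unadjusted contrast is (p_workplace − p_clinic) × δ. With 70 per cell this is (70/140 − 70/140) × δ = 0. The same holds at 56 per cell.

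**5. Two levels, unequal cells (illustrations; the splits are assumed, clinics 70/70).**
- Workplace 100 Stuttgart / 40 Ulm: 0.714 − 0.500 = 0.21 of δ enters the contrast.
- Workplace 110/30: 0.786 − 0.500 = 0.29 of δ.
- Workplace 70/35: 0.667 − 0.500 = 0.167 of δ. If δ were 0.5 SD (assumed), the bias is 0.083 SD. The planned effect is d = 2 × √0.0526 = 0.459 SD, so this is 18% of it.

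The document makes imbalance conceivable. One company has 70,000 employees; for the second, "The other company has about 3,000 employees". Seventy patients are 0.1% of one workforce and 2.3% of the other. Strengths and weaknesses itself lists recruitment in ten months and follow-up dropout as risks.

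**6. Cost of a region term.** With equal cells, type and region have correlation 0 and a variance inflation factor of 1.00. Two-sided 1-df power stays at 92.3% (N = 220), also with region and the interaction both in the model. At the assumed 110/30 split the inflation factor is 1.10.

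**7. What the data can show by region.** With 56 per cell:
- Interaction (difference of differences): SE = √(4/56) = 0.267 SD. For an interaction as large as the planned effect, power = Φ(0.459/0.267 − 1.96) = Φ(−0.24) = 40%.
- Each region's workplace–clinic difference: SE = √(2/56) = 0.189 SD, so a 95% interval of about ±0.37 SD.

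**The case against.** A reader might infer that the pooled contrast is confounded with region. The planned design does not support that: each region supplies both setting types with 70 patients each, so an additive regional effect cancels. Bias needs cells that depart from plan. Because the outcome is change, a stable regional difference in WAI level would drop out of a change score; only a regional difference in change would matter.

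Nor does the document support the 18% in step 5 as an estimate. It gives no uptake rates, does not say which company has about 3,000 employees, and offers no regional difference; the assumed 0.5 SD exceeds the planned effect itself.

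The two-level reading is the better supported one: the sample-size section, the Discussion and the wording of research question 2 all point to it. On the four-level reading region is already in the model, since a four-level factor is the same saturated model as type, region and their interaction. The fault there is only that the 1-df contrast is not named. The 82% also holds total R² at 5%, which the plan assigns to the two-group condition alone; regional differences would raise it. And 82% is low only against the plan's own 95%.

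Finally, this is a condensed article on a self-described explorative study, and factor coding is often left to an analysis plan, which is not available here. That explains missing coding detail. It does not explain using one key term in two senses, or stating a model and a covariate list that leave out a factor of the stated design.

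**Conclusion.** The point holds as a mismatch between design and stated model. The number of levels of the main term for research question 2 is not fixed, and region, one of the two design factors, is not named as a term.

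- If two levels: no bias from an additive regional effect with equal cells, and an exposure that grows with imbalance (0.21 to 0.29 of any regional difference in change under the assumed 100/40 and 110/30 splits). Two workplace offers with different access routes are averaged without any planned look at each.
- If four levels: about 82% power for the omnibus test at N = 220, assuming total R² of 5%, and no direct test of workplace against clinic.

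This is an inexpensive improvement, not evidence that the planned comparison is invalid. A region term cannot separate access route from company or programme age, because these vary together between the two workplaces.

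**What to change.** In the research question 2 paragraph of Statistical analysis, replace the single setting term with two named factors: setting type (workplace, clinic) and region (Stuttgart, Ulm), both effect-coded. State that the primary WAI test is the 1-df type effect averaged over regions, with region as a covariate and the propensity adjustment kept. Effect coding matters: under dummy coding with an interaction in the model, the type coefficient would be the effect in one region only.

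Add the type-by-region term to report the workplace–clinic difference in each region with a confidence interval. Label these as descriptive and draw no conclusion from a non-significant interaction.

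Include region in the research question 1 comparisons in the same way, and use setting with one meaning throughout.

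The cost is wording and at most two degrees of freedom. No extra patients or data are needed, since region is known for every participant.

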### Study design

A mixed methods design [12,13] will be utilized to explore the new care model of "psychosomatic consultation in the workplace" as compared to conventional outpatient clinics. The mixed methods design incorporates a cross-sectional study (research question 1), a second quantitative portion with pre-post comparison (research question 2) (see Figure 1) and a qualitative section (research question 3).

**Figure 1 F1:**
[figure not shown]
**Study design. **Overview of the quantitative part of the study design.

### Sample size and power calculations

Statistical power analyses was conducted with regard to the work ability index (WAI) [14] as primary outcome. In our regression model we assume that the condition „intervention in the workplace/in the psychosomatic clinic“explains a variance of 5%. This means that at a statistical significance of 5% and a power of 95%, we will need 110 participants in each group (workplace and clinic) with a total sample size of n = 220. Bearing in mind a drop out rate of 20% we will include 280 patients.

The quantities for the main question (research question 1) in this explorative study result from the foreseen time schedule during the funding period and the feasibility of recruitment. We expect a high rate of participation since the "psychosomatic consultation in the workplace" so far has been greatly accepted and appreciated by the employees. In addition, the employees are assured that the collected data will be kept confidential under the supervision of the research group at the university. To increase the response rate for the follow-up survey, there will be a reminder mailing or a phone call.

There are 14 variables to be measured. The two intervention groups consist of employees who use this service within the 10 month recruitment period. One company has a total of 70,000 employees at the participating sites. The other company has about 3,000 employees. The ratio of male to female employees in both companies is about 4:1 with an average age of 43 years. The employees are unevenly distributed to work in research, development, production and administration.

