### Statistical analysis

Research question 1 : *Are there differences in demographic, clinical and psychometric characteristics between patients who use the consultation offer in the workplace* versus *patients who use the established outpatient care?*

The differences between treatment groups will be examined by means of logistic regression analysis (in the form of binomial and multinomial models) including age, sex, educational level, occupational category, using the number of previous contacts with psychiatric-psychosomatic services as independent variables. The results of the logistic regression models will be used to estimate the propensity scores for the conditional probability of being referred to a particular treatment group.

The factors of interest of research question 1 are the type and severity of the disease (PHQ) the duration of symptoms, the health-related quality of life (SF-12), work ability (WAI), work-related stress effects (MBI, IS), work requirements (KFZA), the number of previous contacts with the mental health care system as well as demographic factors (Table 1). The demographics may be incorporated to the model independently or in terms of propensity scores.

By using multivariate analysis (latent class analysis = LCA) techniques it is possible to discern which patients with specific combinations of traits fit into certain clusters and determine the effect the particular setting has on the patients’ assignment in each particular cluster. The multivariate analysis is performed using the General Mixture Model (GMM) approach [21,22]. The basis here is the relationship between various characteristics of a limited number of categorical latent classes. The number of latent classes can be determined via various statistical methods (Bayesian Information Criterion, Akaike Information Criterion, Lo-Mendel-Rubin Test). By extending this model to a conditional latent class model, the effects of covariates on the likelihood of class membership can be estimated. The covariates in this study are the respective treatment settings, demographic data and job-specific characteristics of the responders.

Research question 2: *What are the changes 12 weeks after initially using the offer "psychosomatic consultation in the workplace" and how are they different from those in the control group?*

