### Inclusion criteria

The only inclusion criterion is that the respondents must be at least 18 years of age. Other inclusion criteria are not relevant since we are recruiting consecutively and this is an explorative study.

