### Strengths and weaknesses

The main strength of our study is that, except for one non-empirical article [11], there is little data in this field. We will evaluate whether or not we will reach different types of patients if we, as health professionals, initially see patients at their workplace and not within the traditional setting of a psychosomatic outpatient clinic. The best way to investigate this question is an explorative design with consecutive recruitment of patients. Therefore, we do not match groups for age, gender or desease severity.

A disadvantage of the explorative design is the inability to compute effect sizes. To be able to obtain utilization data of our model under routine conditions, we decided to choose a non-randomized controlled design. Another limitation of the study is the recruitment of a sample size of 280 participants in the allotted time of 10 months. Most studies in this field have problems recruiting participants. In contrast to the other studies, however, we expect a high rate of participation because the "psychosomatic consultation in the workplace" has been appreciated and well-received by the employees so far. In addition, the employees are assured that the collected data will be kept confidential under the supervision of the research group at the university. Another critical issue might be a high dropout rate at follow-up which we will attempt to minimize with a reminder phone call, email or letter. A long-term follow-up survey (i.e. at 6 months after T1) would be reasonable, but cannot be realized within the funding period. We plan to investigate this issue in a future project.

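### The workplace–clinic contrast in research question 1 describes case mix, but cannot show that a demographic difference is due to the place of first contact

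*Protocol article*

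**What the plan says.** The Background section of the protocol article poses research question 1 as a comparison against clinic patients: "Are there differences in demographic, clinical and psychometric characteristics between patients who use the consultation offer in the workplace". The Abstract lists demographic characteristics among the differences of main interest.

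The sources of the two groups are described in separate places:
- Workplace (Sample size and power calculations): "The two intervention groups consist of employees who use this service within the 10 month recruitment period". The same paragraph gives the workforces as roughly 70,000 and 3,000 employees and adds: "The ratio of male to female employees in both companies is about 4:1 with an average age of 43 years".
- Clinic (Inclusion criteria): "The only inclusion criterion is that the respondents must be at least 18 years of age".
- Comparability (Strengths and weaknesses): "Therefore, we do not match groups for age, gender or desease severity".

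The Statistical analysis section plans logistic models of treatment group with age, sex, education, occupational category and earlier service contacts as independent variables. It also plans a latent class analysis meant to "determine the effect the particular setting has on the" cluster to which a patient is assigned. Strengths and weaknesses states the intended inference: "We will evaluate whether or not we will reach different types of patients if we, as health professionals, initially see patients at their workplace" rather than in a clinic. The workforce figures are not used in any planned analysis.

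**The concern.** Two things determine the demographic make-up of the workplace group: whom the companies employ, and which of those employees choose, or are referred to, the consultation. Only the second says anything about selective reach of the offer. The planned contrast with clinic patients sees the two combined, and sets them against a group drawn from a different, wider population.

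Adjustment does not separate them. For the demographic part of the question, sex, age and occupation are the characteristics being compared, so they cannot also be adjusted away. In a logistic model of setting, the sex coefficient carries the sex ratio of the source populations. The same holds for a latent class defined partly by demographic traits.

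At stake is the interpretation of the demographic findings and class profiles. A large, clearly significant sex difference could be presented as the workplace location reaching a different kind of patient, when it may reflect only the composition of two industrial workforces.

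**Working it through.** **Inputs from the article.** A workforce ratio of 4:1 gives a male share of 4/5 = 0.80 and male odds of 4. Four settings with 70 patients each give 280, so 140 workplace and 140 clinic patients at baseline. The article's power calculation concerns the work ability index and does not bear on this point. It says the numbers for research question 1 follow from the funding schedule and feasibility, so there is no planned figure to reproduce here.

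**Assumptions.** The clinic male share c is not in the article and is varied. The uptake of women relative to men among employees, k, is hypothetical: k = 1 means use unrelated to sex.

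**Formulas.**
- Male share of users: m = 0.8 / (0.8 + 0.2k). For k = 1, m = 0.80. For k = 2, m = 0.8/1.2 = 0.667.
- Workplace–clinic odds ratio for being male: OR = (4/k) / (c/(1 − c)).
- z = (m − c) / √[(m(1 − m) + c(1 − c))/140].

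The odds ratio formula shows the difficulty. The workforce factor 4 and the selection factor 1/k enter only as a product, so workplace and clinic data alone cannot recover k.

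| Assumed clinic male share | OR, k = 1 | z, k = 1 | OR, k = 2 | z, k = 2 |
|---|---|---|---|---|
| 0.35 | 7.43 | 8.55 | 3.71 | 5.59 |
| 0.40 | 6.00 | 7.48 | 3.00 | 4.64 |
| 0.50 | 4.00 | 5.54 | 2.00 | 2.87 |
| 0.60 | 2.67 | 3.74 | 1.33 | 1.16 |
| 0.65 | 2.15 | 2.85 | 1.08 | 0.29 |
| 0.70 | 1.71 | 1.95 | 0.86 | −0.60 |
| 0.80 | 1.00 | 0 | 0.50 | −2.55 |

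With k = 1 there is no selective use by sex. Even so, the probability of a two-sided p < 0.05 is about 100% for clinic shares up to 0.50, then 96%, 81% and 49% at 0.60, 0.65 and 0.70.

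**The same users against their workforce**, treating the workforce share of 0.80 as known:
- k = 1: share ratio 0.80/0.80 = 1.00. For one company (n = 70), the standard error of m is √(0.16/70) = 0.048, so the 95% interval for the ratio is about 0.88 to 1.12.
- k = 2: share ratio 0.667/0.80 = 0.83. Against the workforce share, z = −0.133/√(0.16/140) = −3.9 for both companies together, and −0.133/√(0.16/70) = −2.8 for one company.

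The share ratio therefore isolates selective use by sex, and at the planned size it can detect a twofold difference in uptake even within one company.

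**The case against.** The strongest reply is that research question 1 is descriptive. If one setting sees mostly men and the other does not, the two settings do see different patients, and that is an answer, not an artefact. Placing a consultation in an industrial plant partly consists of gaining access to that plant's workforce. This stands: the clinic is the right comparator for describing case mix.

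A reader might go further and infer that the plan will conclude that the offer reaches men better, or will conclude the reverse of the truth if women use it more. The article does not support that. It states no hypothesis on uptake by men and women among employees, and its explicit wording on reaching employees, in research question 1, concerns being earlier in the illness. The size and direction of the contrast also depend on a clinic sex mix that the article does not give.

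The workforce benchmark has limits too. Headcount is not need: if mental health problems are more frequent in one sex, unequal uptake may be proportionate. Employees in Stuttgart are mainly referred by occupational physicians or the social worker, so a ratio there partly reflects referral. Absolute uptake is uninformative, because the target of 70 per setting fixes it at about 70/70,000 = 1.0 and 70/3,000 = 23 per 1,000.

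What remains is that the effect wording for the latent classes, and the stated aim of learning whom one reaches by going to the workplace, go beyond case mix. The planned contrast cannot carry that step for demographic traits.

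**Conclusion.** The point holds as a limit on interpretation. The workplace–clinic contrast validly describes who attends each setting. It does not show that a demographic difference, or a demographic class profile, arises from the place of first contact.

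If use is unrelated to sex, the composition of the workforces alone gives an odds ratio of 7.4 to 4.0 for an assumed clinic male share of 35–50%, falling to 1 as that share approaches 80%. Misreading is therefore possible, and likely over much of the assumed range, but not certain. The calculation rests on the stated 4:1 ratio applying to each company, 140 per group, and the assumed clinic share.

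The clinical comparisons are largely unaffected, since the plan allows demographics to enter those models directly or through propensity scores. This is an inexpensive improvement that uses a reference the study already partly holds.

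**What to change.** In the Statistical analysis section, under research question 1:
- Add, for each company separately, the ratio of the users' share to the workforce share by sex and by age band, with confidence intervals. Do not report absolute uptake per 1,000 employees.
- Base any statement about selective reach by sex or age on that ratio.
- Label the workplace–clinic demographic contrast as a description of case mix.
- Word the relation between setting and latent class assignment as an association, not an effect, and bring the corresponding sentence in Strengths and weaknesses into line.

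The cost is a few sentences and one table, plus aggregate headcounts by sex and age band from the two companies, whose totals, sex ratio and mean age are already reported. Recruitment and questionnaires do not change. The report should state the remaining limits: the benchmark is one-sided because the clinics have no equivalent, headcount does not measure need, and the Stuttgart ratio also reflects referral.
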